## Background

Accounting for $46-billion - or 36% of public spending on health care [1] - hospitals are a major target for cost reductions through efficiency initiatives in Canada. Some provinces are considering payment reform as a vehicle to achieve this goal. The use of financial incentives to increase hospital efficiency is now widespread in Europe and has occurred in the United States (US) since 1983 [2-4]; however, the approach remains largely untested in Canada [5].

In April 2010, the British Columbia (B.C.) provincial government implemented activity based funding (ABF) for hospitals, marking a fundamental change to the method of funding acute hospital care. ABF will direct up to 20% of available funds to acute hospitals on the basis of types and volume of services. This change is significant in an industry accustomed to historically-based global budgets and unaccustomed to detailed scrutiny of what services are provided to B.C.'s 4.5 million residents and at what cost.

While this change in hospital funding is being implemented in B.C., a debate over the relative merits of hospital ABF is unfolding across Canada [6,7]. For example, the Canadian Medical Association and the B.C. Medical Association have recently staked positions supportive of ABF [8-10], although support for ABF among the medical community is mixed [11,12]. The Canadian Nurses Association supports an increasing emphasis on output measurement [13] but falls short of endorsing ABF, while other groups are calling for more comprehensive baseline data [14]. Although there has been no formal examination of the effects of ABF policies in Canada - in part because B.C. is the first province to adopt ABF for acute hospitals on a large scale - several other provinces are considering adopting similar funding models.

This project will provide an evidence base on the impacts of ABF, including changes in the type, volume, cost, and quality of services provided. Policy- and decision-makers in B.C. and elsewhere in Canada will be able to use this evidence as a basis for policy adaptations and modifications.

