Previous studies have not rigorously examined the non-hospital effects of changing acute hospital payment methods, and it is not known how the change to ABF will affect the demand for home care or the ability to maintain high quality home care services. We will calculate the number of new home care patients each month using the continuing care dataset, looking retrospectively to determine which patients are 'new' to home care as opposed to existing patients. Changes in the trend of the number of new home care patients will provide valuable insight into the acuity of patients discharged from acute care. Based on the cohort of home care patients, we will then calculate the number of readmissions to acute care from home care over time. This important signal of care quality may suggest increased pressure on home care services attributable to ABF.

To date, no published information describes the nature of change in use of physician services after implementation of ABF. Medical Services Plan data allow us to determine the amount of all fee-for-service physician payments. For each acute discharge, we will link the amount of physician payments in the 30-day period following the incident discharge (including readmissions). Total physician expenditures will be linked to hospital data and registry data to enable our analytic dataset to be able to be analyzed over time and for specific conditions (see Table 3). To isolate changes of physician utilization from physician payments over time, we will draw on work currently being undertaken at the Centre for Health Services and Policy Research (CHSPR) on a separate study to remove the effects of fee changes from physician fees.

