### Data Resources and Variable Construction

The analytic dataset for **Aim 1 **(*internal to the hospital*) will be derived from acute and outpatient DAD hospitalizations linked to the registry data. The dataset will include the following variables: month and year of discharge, CMG, CIHI-defined age group, hospital, region of residence (HA), length of stay (LOS), ICD-10-CA codes, indicator of death, and Adjusted Clinical Groups (a measure of health status [28]). The number of inpatient separations per year, for the conditions to be studied (Table 1), is expected to exceed 5,000. We will analyze hospital separations over the period from fiscal year 2005/2006 through to, and including, 2012/2013, to ensure consistent application of CMG+ across all years.

We will consider the effect of data quality and completeness on the results. The most recent multi-stage randomized studies of DAD data quality, which involve clinical chart re-abstractions, have been conducted by CIHI and have found the majority of data elements in the DAD are accurately reported [35], with comorbidity reporting being an important exception. We will use the results of these studies to exclude those ICD-10-CA codes susceptible to being affected by coding practice changes. Further, we will link Medical Services Plan data to hospital separation data to evaluate completeness of reporting (a means to validate procedure information in the DAD).

One comprehensive analytic dataset will be created for **Aim 2 **(*external to the hospital*) for the years 2005/2006 through 2012/2013. This analytic dataset will be the product of linking acute hospital, registry and continuing care datasets with summarized physician fee-for-service expenditure data. The hospital data will be used to calculate rates of: readmission, admissions from the emergency department and ambulatory care sensitive admissions. The analytic dataset will include admission date, CMG, hospital, region of residence, ICD-10-CA codes, procedure date and whether the patient was admitted from the ED. Readmissions at separate hospitals will be attributed back to the incident hospitalization. The analytic dataset will include an indicator variable to represent incident cases of new home care in the period immediately following discharge from acute care. A variable representing the amount of physician services will be determined from the physician fee-for-service Medical Services Plan (MSP) data linked to patient data.

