The parameters of interest are those associated with immediate change in the number of deaths (relative to the number of discharges, *N*_*i*_) and a change in the trend of number of deaths. We will explore the use of zero-inflated Poisson (ZIP) models if we find an abundance of counts of 0.

Similar to the approaches described above, we will use a linear regression model (suitably transformed for normality) to detect changes in hospital expenditures associated with ABF implementation (including adjustments for effects of inflation) and controlling for repeated measures on hospitals.

Following published methods for calculating hospital readmission rates [31], we will calculate overall readmission rates using a multivariate Poisson model for count data, controlling for repeated measures on hospitals. We will also construct separate models for the conditions listed in Table 3. The regression models of monthly hospital readmission rates will include effects for hospital, time and a binary variable for ABF. The parameters of interest represent immediate change in readmission and change in trend over time.

We will use a linear regression model to examine the relationship between the number of (monthly) new home care patients and ABF. The unit of observation will be the number of new home care patients within an HA and we will control for repeated measures over time. The effects of primary interest are those associated with immediate change in new home care patients and a change in the trend of home care patients. Given stable monthly count data at the HA-level, we expect to be powered able to detect moderate and large sized effects.

Similar to the methods described above, we will model the number of monthly readmissions to acute care from home care using a Poisson model for count data and adjust for HA and hospital effects. The parameters of interest are those associated with immediate change in the number of readmissions to acute care from home care and a change in the trend of number of readmissions.

We will also use a log-transformed model to examine the association between patients' fee-for-service physician expenditures (fee-adjusted) over time, and implementation of ABF. The regression equation for patients' fee-for-service, fee-adjusted, physician expenditures is written:

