where the parameters of interest are change in level (θ) and change in trend (τ). The vector ***X***_***i ***_will include effects to control for repeated measures on physicians and hospitals plus will adjust for patient level effects, such as age and comorbidity burden (derived from CMG).

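### The physician-expenditure model names physicians and hospitals as the repeated units, but its outcome is a per-discharge patient total, so the physician effect has no defined unit and repeat discharges of one patient are not modelled

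*Protocol article*

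**What the plan says.** The outcome is defined under Aim 2 in the Design section of the protocol article: "For each acute discharge, we will link the amount of physician payments in the 30-day period following the incident discharge (including readmissions"). The same paragraph treats the amount as a sum: "Total physician expenditures will be linked to hospital data and registry data". Data Resources and Variable Construction describes the Aim 2 file as a linkage of hospital, registry and "continuing care datasets with summarized physician fee-for-service expenditure data".

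The Analysis section proposes a log-transformed model to "examine the association between patients' fee-for-service physician expenditures (fee-adjusted) over time, and implementation of ABF". It introduces the equation with "The regression equation for patients' fee-for-service, fee-adjusted, physician expenditures is written" and continues "where the parameters of interest are change in level (θ) and change in trend (τ"). The covariate vector "will include effects to control for repeated measures on physicians and hospitals plus will adjust for patient level effects, such as age and comorbidity burden".

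On hospital clustering, the Analysis section says of the case-mix volume model that it is handled by putting hospital effects into the covariate vector. The expenditure model is worded in the same way.

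**The concern.** The repeated units named in the model do not match the outcome being modelled.

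- **Physician.** One 30-day total can include payments to a surgeon, an anaesthetist, a family doctor and others. A repeated-measures effect for physicians needs each observation to belong to one physician, or a stated way to share it among several. The article gives neither.
- **Patient.** The person discharged is the unit that can recur. Age and comorbidity adjust the mean. They do not remove the correlation left between two discharges of a person who uses more, or less, physician care than the covariates predict.

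At stake are the standard errors of θ and τ, on which the inference for Hypothesis 2.3 rests. If they are too small, a chance shift in physician spending could be reported as an effect of activity based funding (ABF).

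**Working it through.** **No figure to reproduce.** The article states no alpha, power, SD, stays per patient or within-patient correlation for Hypothesis 2.3. The check therefore asks how far the reported SE could be from the true SE over a range of assumptions.

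**Inputs from the article.** Fiscal years 2005/2006 to 2012/2013 give 8 × 12 = 96 months. The policy start is given in Background: "In April 2010, the British Columbia (B.C.) provincial government implemented activity based funding (ABF) for hospitals". April 2010 is month 61, so there are 60 months before and 36 after. Parameters: θ and τ.

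**Assumptions, not in the article.** Stays per patient are 1 + Poisson, with mean 1.3, 2 or 3. Within-patient correlation ρ is 0.1, 0.3 or 0.5 on the model scale. There are 40 hospitals, and each patient stays in one of them. Discharges are spread over the 96 months, or bunched within 12 or 3 months.

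**Method.** Regress on time, policy and time since policy, with hospital effects. Let X be the design after hospital means are removed, and V the true correlation matrix (ρ between discharges of the same patient). With A = (X′X)⁻¹, the reported variance is proportional to A and the true variance to A(X′VX)A. The ratio of true to reported SE is the square root of the ratio of their diagonal elements.

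| Timing of a patient's discharges | Level θ | Trend τ |
|---|---|---|
| Spread over 96 months | 1.00 | 1.00 |
| Within 12 months | 1.02 to 1.34 | 1.02 to 1.45 |
| Within 3 months | 1.02 to 1.48 | 1.03 to 1.53 |

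Each range runs from mean 1.3 stays with ρ = 0.1 to mean 3 stays with ρ = 0.5. In the spread case all values lie between 0.996 and 1.003.

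**Hand check of the top value.** If all of a patient's discharges fell in the same month, the variance would inflate by 1 + (m* − 1)ρ, where m* = E(k²)/E(k) and k is the number of stays. For k = 1 + Poisson(2), E(k) = 3 and E(k²) = 2 + 9 = 11, so m* = 11/3 = 3.67. At ρ = 0.5 the factor is 1 + 2.67 × 0.5 = 2.33, and √2.33 = 1.53, which agrees with the table. When discharges are spread at random, one discharge's timing says nothing about the next, the cross-products average to zero, and the ratio is 1.

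**Effect on the test.** A two-sided 5% test whose SE is too small by a factor r rejects under no effect with probability 2[1 − Φ(1.96/r)]: 14% at r = 1.34, 18% at 1.45, 19% at 1.48 and 20% at 1.53. A simulation of the worst corner (mean 3 stays, ρ = 0.5; 400 runs, so a simulation error of about 1 point near 5% and 2 points near 20%) gave:

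| Timing | Independent residuals, θ / τ | Variance clustered on hospital, θ / τ |
|---|---|---|
| Spread | 4.0% / 3.3% | 5.5% / 3.3% |
| Within 12 months | 14.5% / 18.8% | 5.3% / 6.5% |
| Within 3 months | 20.3% / 22.5% | 6.3% / 7.8% |

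Clustering on hospital thus removes most of the deficit when patients return to the same hospital.

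**The case against.** The strongest reply is that nothing here proves the intervals wrong. The article is a condensed account, its equation is not visible in the text at hand, and its list of patient effects is open-ended. It does not say whether the hospital control is a fixed effect, a random effect or a robust variance. A hospital-clustered variance would bring the test close to 5%, and with spread-out discharges there is no deficit. An attribution rule, such as a most responsible physician, could also sit in a fuller plan, and the article does intend to identify physicians paid mainly by fee-for-service.

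Much of this stands. A reader might infer that the Hypothesis 2.3 standard errors are certainly too small. The documents do not support that, because they fix neither the recurrence pattern nor the variance method. Nor is the patient left out altogether: what is absent is a patient-level repeated-measures term.

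A reader might also infer that a readmitted patient's payments are counted twice, in overlapping windows. The article does speak of every acute discharge. But it also calls it the incident discharge, includes readmissions in its total, and in Data Resources credits readmissions elsewhere to the incident stay. The more natural reading is that readmissions fold in. The rule needs stating, but double counting is not shown.

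The mismatch itself remains. Identifying physicians does not assign a multi-physician total to one of them. The wording on hospital effects points towards effects in the covariate vector, which leave within-patient correlation in the residuals. And the article expects some readmissions at other hospitals, so the single-hospital assumption behind the favourable result will not hold for everyone.

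**Conclusion.** The point holds as a mismatch of units with a possible, not certain, effect on precision. The physician effect has no defined unit in a model of per-discharge patient totals, and the patient has no repeated-measures term.

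If hospitals enter as effects with independent residuals, the SEs of θ and τ may be too small by a factor between 1.0 and about 1.5. The upper end needs mean 3 stays, correlation 0.5 and discharges within 3 months. With mean 2 stays, correlation 0.3 and discharges within 12 months, the factors are 1.13 for θ and 1.17 for τ. All these inputs are assumptions. The clustered-variance result further assumes that patients do not change hospital. This is a correction worth making before analysis, not grounds to reject the plan for Hypothesis 2.3.

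**What to change.** 1. State the incident discharge as the unit of analysis.
2. Drop the physician repeated-measures effect from this patient-total model. If inference about physicians is wanted, analyse physician-level payments separately.
3. Keep the hospital effects and cluster the variance on patient and hospital. Clustering on hospital alone is an acceptable alternative, with a check for patients who change hospital.
4. State that a readmission inside an open 30-day window belongs to that window and opens none of its own, and that a later discharge may open a new window once the earlier one has closed. No payment is then counted twice.

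A stricter rule that requires 30 days clear of any acute discharge should be avoided. With discharges on days 0, 25 and 50 it would open only the first window and never count payments from day 30 to day 80, and eligibility would depend on readmission, which ABF may change. Under the rule in step 4, day 50 opens its own window. Payments between days 30 and 50 fall in neither window, which should be acknowledged.

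The cost is a change of wording and an index-discharge flag from data already linked. Intervals become slightly wider, and a small share of discharges stop being separate observations.

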## Discussion

The examination of hospital and non-hospital effects of the implementation of ABF in B.C. is both critical and timely given the high public profile of the "sustainability" of the health care system, the large cost footprint represented by acute care hospitals, and the mushrooming interest in ABF across Canada. For the MoHS, the policy rationale for ABF - to increase hospital efficiency while holding the line on aggregate expenditures - is clear: regional HA block operating grants fail to create the incentives for hospital-derived efficiencies that ABF may provide.

If B.C.'s policy-makers are to assess the extent to which their objective of increasing hospital efficiencies without sacrificing quality has been achieved, it is critical that they be able to monitor effects of ABF on a timely basis. While from a policy perspective, this proposed work will help position the MoHS to ensure its objectives are met, the overall goal of this research is to examine the impact of ABF not just on hospital activity, but more broadly on the health care system overall.

### Study Limitations

While we are leveraging the natural experiment of a significant change in hospital funding, we are limited in the type of study design we can use. Since the MoHS' ABF initiative includes all hospitals, it is not possible to 'randomize' hospitals to ABF and non-ABF groups as to isolate the effect of the implementation of ABF. We are not including another province's hospitals to act as a 'control' group due to the potential confounding from reporting differences between provinces, hospital funding policy changes in other provinces and the potentially insurmountable problems associated with, but undoubtedly lengthy time required to, securing data access in multiple provinces. Given these constraints, a longitudinal design is the strongest possible design. Our study will be limited to administrative datasets, precluding the use of detailed clinical data that might inform our analyses.

### Potential Contributions and Significance

This project represents a unique opportunity to examine the health care system during a time of significant policy change in B.C. that will have implications for health system funding across Canada. This project will lay a solid foundation upon which to build future projects, including the development and integration of outcome and quality indicators into health system performance measurement in B.C.

This study represents a unique opportunity to leverage the natural policy experiment occurring in B.C. and will contribute to understanding the dynamics underlying the most significant and expensive segments of our health care system. By the end of the study, we expect to propose a series of policy recommendations as they relate to monitoring health system use within a new framework for hospital funding. The insight gained from these activities will be of high value to all Canadians.
